### Study Design

#### Cluster Randomized Trial Design

Forty rural health facilities and their catchment areas (*clusters*), 20 per region, will be randomized to an (A) early or (B) delayed onset study arm (Figure 2). From each cluster, 3 cohorts of 10 mother-child dyads (1 retrospective cohort and 2 prospective cohorts) will be enrolled into the study. For the retrospective cohort, 400 mothers of children aged 12 to 23 months (10/cluster) will be enrolled as a cross-sectional sample for retrospective assessments of children’s vaccination records during the first year of life. These cohorts, denoted by A1 and B1, will be part of the care-as-usual control group. For the longitudinal prospective cohort, 800 pregnant women in their last trimester of pregnancy will be enrolled during 2 rounds of enrollment (10 women/enrollment round/cluster) for prospective assessments of their children’s vaccination records during the first year of life. These cohorts are denoted by A2, A3, B2, and B3. In the first round of enrollment, 200 (50%) of the 400 prospective participants (those enrolled from early onset clusters; A2) will receive the intervention, and the other 200 (50%) participants (B2) will be part of the care-as-usual control group. In the second round of enrollment, all 400 participants (A3 and B3) will receive the intervention. In total, vaccination uptake and timeliness will be observed for 1200 children (n=600, 50% intervention group children and n=600, 50% nonintervention group children) during their first year of life. The nonintervention group children represent the *care-as-usual* control group in the trial.

The trial design, which analytically resembles a difference-in-difference design, allows for an analysis of the effectiveness of the intervention even in the context of contemporaneous changes in the rate and timeliness of vaccinations at the national level (eg, through national vaccination campaigns or changes in the vaccination schedule).

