### Statistical Power

The aim 1 cluster randomized trial will include 1200 women, enrolled from 40 different clusters, across 3 distinct enrollment phases, with 10 women enrolled from each cluster in each phase. This equates to k=120 statistical clusters with n=10 women per cluster. Half of these clusters (k=60/120, 50%; n=600/1200, 50%) will be allocated to the intervention arm and half to the control arm. Assuming that the primary outcome—the timeliness of the Penta3 vaccine—has an SD of 28 days, the power of the trial to detect an intervention-related difference of 7 days is 0.95 with an intracluster correlation coefficient of 0.05; the power is 0.88 with an intracluster correlation coefficient of 0.10.

The aim 2 qualitative formative work will yield data from IDIs with key informants (n=12), facility-based health workers (up to n=40), CHWs (up to n=80), and mothers (up to n=60). Prior research suggests that thematic saturation can be achieved with 12 interviews, with metathemes presenting as early as 6 interviews [23-25]. Thus, these proposed sample sizes should be sufficient to achieve thematic saturation of implementation barriers and residual barriers to timely and equitable vaccinations, as well as to identify any regional variation in reasons for delayed vaccinations.

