### Data Analysis

#### Quantitative Analysis of Intervention Effectiveness

The primary outcome measure of interest will be a continuous measure of vaccination timeliness, expressed as the delay, in days, between the vaccination due date and the date on which the vaccination was received for the third dose of the pentavalent vaccine, Penta3, due at age 14 weeks (Table 1). The secondary and other outcome measures include the timeliness and coverage of all vaccine doses recommended by age 1 year. Owing to the randomization, a comparison of mean outcomes between participants in the intervention group and those in the nonintervention group yields an unbiased estimate of the effect of the intervention.

To control for variation in sociodemographic characteristics across participants, seasonal effects, and other potential correlates of vaccination timeliness, outcomes will also be analyzed in a multivariable regression framework using accelerated failure time models with the completed vaccination dose as the failure event, age in days describing time to failure, and membership in the intervention versus control groups as the primary covariate of interest.

Robust SEs will be estimated to account for the clustering of observations across mother-child dyads enrolled from the same geographic clusters at the same time.

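### Each facility's pre-intervention Penta3 delay is collected, but the named analyses contain no facility, facility-baseline or enrollment-phase term; the cost is small in the planned pooled contrast and appreciable once phase is modelled

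*Protocol article*

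**What the plan says.** Under Cluster Randomized Trial Design, 40 facilities are randomized to early (A) or delayed (B) onset, and each contributes three cohorts of 10 dyads. The retrospective cohort (children aged 12 to 23 months, 400 in all) is handled as follows: "These cohorts, denoted by A1 and B1, will be part of the care-as-usual control group". In the first prospective round A2 receives the intervention and B2 does not; in the second, A3 and B3 both receive it. The same section adds: "The trial design, which analytically resembles a difference-in-difference design", and presents this as protection against contemporaneous national changes in vaccination.

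Under Quantitative Analysis of Intervention Effectiveness, the article argues from randomization that "a comparison of mean outcomes between participants in the intervention group and those in the nonintervention group yields an unbiased estimate" of the effect. It then describes an accelerated failure time model with "membership in the intervention versus control groups as the primary covariate of interest", adjusted for sociodemographic characteristics, season and other possible correlates of timeliness. Robust standard errors are clustered by geographic cluster and enrollment time together. No facility effect, facility baseline delay, enrollment phase or arm-by-phase term is named.

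**The concern.** A1 and B1 give a card-based measurement of the primary outcome in every randomized unit before the intervention starts. With 20 facilities per arm, facility differences contribute materially to the error of the randomized comparison, and a baseline of this kind can remove part of it. The design section describes a structure in which A1/B1 would be the pre-period; the analysis section puts them into the control group and uses them no further.

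Two things are at stake. First, precision: an available baseline goes unused. Second, coherence: the promised protection against time trends needs phase in the model. Once phase is there, how the facility baseline is used decides how much of the 1200-child sample informs the effect. A reader who took the difference-in-difference remark literally and subtracted the A1-B1 difference would in most settings lose precision rather than gain it.

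**Working it through.** **Inputs.** From Statistical Power: outcome "has an SD of 28 days", effect 7 days, 120 facility-by-phase cells of m = 10, 60 per group. From the design section: 20 facilities per arm; treatment pattern over the three phases A = 0,1,1 and B = 0,0,1. Assumed: two-sided 5% (not stated, but it reproduces the stated powers), and the cluster autocorrelation (CAC), meaning the correlation of a facility's effect between two cohorts. The article gives no CAC; 1, 0.8 and 0.5 are shown. Power = Φ(7/SE − 1.96) throughout.

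**1. The plan's own figures.** DEFF = 1 + 9·ICC, which is 1.45 or 1.90. SE = 28·√(2·DEFF/600) = 1.95 or 2.23. Power = 0.949 or 0.881. The article states that power "is 0.95 with an intracluster correlation coefficient of 0.05" and that "the power is 0.88 with an intracluster correlation coefficient of 0.10"; both reproduce. They describe the pooled contrast A2+A3+B3 versus A1+B1+B2 with 120 independent cells.

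**2. Chance facility imbalance.** The SD of the early-minus-delayed difference in true facility means is √(2·ICC·784/20) = 1.98 days (ICC 0.05) or 2.80 days (ICC 0.10). Early facilities supply 400 of 600 treated and 200 of 600 control children, so 400/600 − 200/600 = 1/3 of a stable difference reaches the pooled estimate: SD 0.66 or 0.93 days. In A2 versus B2 all of it does.

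**3. Pooled contrast, no phase terms.** Per facility, a cell mean has variance 784·(ICC + (1−ICC)/10) and two cells have covariance 784·ICC·CAC. Power of the plain mean difference, then with a random facility effect:

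| | CAC 1 | CAC 0.5 |
|---|---|---|
| ICC 0.05 | 0.984 to 0.990 | 0.969 to 0.972 |
| ICC 0.10 | 0.974 to 0.992 | 0.933 to 0.944 |

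The gain is about 0 to 2 points. The true pooled SE (1.71 to 1.83 at ICC 0.05, 1.80 to 2.02 at ICC 0.10) lies below the plan's 1.95 and 2.23, because the same facilities supply treated and control children.

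**4. With phase terms.** In phases 1 and 3 both arms have the same treatment status. A least-squares fit with phase terms and no facility term therefore estimates the effect from A2 versus B2 only: SE = 28·√(2·DEFF/200) = 3.37 or 3.86, power 0.55 or 0.44.

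Three ways of using the facility information, power at CAC 1/0.8/0.5:

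| Method | ICC 0.05 | ICC 0.10 |
|---|---|---|
| None (A2 versus B2) | 0.55 | 0.44 |
| Phase effects plus random facility intercept, all 1200 | 0.63/0.60/0.57 | 0.62/0.55/0.49 |
| A2 versus B2 adjusted for facility A1/B1 mean | 0.60/0.58/0.56 | 0.57/0.52/0.47 |
| Plain subtraction of A1-B1 | 0.44/0.41/0.37 | 0.46/0.39/0.32 |

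Row 2 is generalized least squares with the covariance in step 3; SE 3.06/3.16/3.29 and 3.08/3.34/3.64. Row 3 multiplies the variance of A2 versus B2 by 1 − r², with r = 10·ICC·CAC/DEFF (at CAC 1, r = 0.345 or 0.526). Row 4 multiplies it by 2(1 − r), which is below 1 only when r exceeds 0.5; among the settings shown that happens only at ICC 0.10 with CAC 1.

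**The case against.** The strongest reply is that the planned contrast is not short of power. A reader might infer that the trial's stated analysis loses power by ignoring the baseline; step 3 shows it loses at most about 2 points. The larger gains appear only after phase terms are added, which the article does not propose. This stands, and it limits the point. It does not remove it, because A1/B1 are all untreated and A3/B3 all treated: randomization by itself supports only A2 versus B2, and protection against secular change requires phase in the model.

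A reader might also infer that chance facility imbalance biases the estimate. It does not. It is random error, and two thirds of a stable difference cancels in the pooled contrast.

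Third, one might say that A1/B1 serve as nothing but extra controls and that every model excludes the baseline. The difference-in-difference remark and the open-ended reference to other correlates do not support so absolute a reading, and a full covariate list may sit in an analysis plan that is not shown. Still, the article does commit to an estimator, justifies it by randomization and powers it; the structure described in its design section is absent from that estimator.

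Fourth, the Cluster Randomization and Randomization sections allow covariate-constrained randomization, with vaccination coverage among the listed characteristics. This helps, but it is conditional on observed imbalance and does not list Penta3 delay.

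Finally, CAC 1 is optimistic: A1/B1 are recruited after the first birthday and A2/B2 in pregnancy, from different birth periods.

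**Conclusion.** The point holds as a worthwhile improvement rather than an error that undermines the trial. Design and analysis sections do not match: a facility-level pre-intervention outcome and a difference-in-difference rationale are described, and the named analyses use neither. In the pooled contrast as planned, the consequence is about 0 to 2 power points and a random error of SD 0.66 to 0.93 days against a 7-day target. In a phase-adjusted analysis, a random facility intercept is worth roughly 2 to 8 points at ICC 0.05 and 4 to 18 points at ICC 0.10. The upper ends require a CAC of 1.

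These figures rest on the plan's SD and ICCs, two-sided 5%, 10 children in every cell, a normal approximation and the assumed CAC. No form of baseline adjustment brings phase-adjusted power back to 0.95 or 0.88; the best figure here is 0.63.

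**What to change.** In Quantitative Analysis of Intervention Effectiveness, specify that the effect is estimated on all 1200 children with enrollment phase as fixed effects, a random intercept for facility and a facility-by-phase random effect, using a small-sample correction suited to 40 facilities. In the accelerated failure time model, add a facility frailty term or the facility's A1/B1 mean Penta3 delay as a covariate. State that the baseline enters through the random effect or as a covariate and not by subtracting A1-B1.

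Adjusting A2 versus B2 for the facility's A1/B1 mean is a simpler alternative, but it is less efficient (at CAC 1, 0.60 against 0.63 and 0.57 against 0.62) and should not be described as equivalent.

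The cost is analysis wording and slightly more modelling; no further data are needed. The gain shrinks if facility timeliness is not stable between cohorts. The power statement should be restated for whichever model is adopted.

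### Robust standard errors are clustered on facility-by-round (120 cells) rather than on the 40 randomized facilities, so the intervals are generally miscalibrated, by an amount and in a direction that depend on the model

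*Protocol article*

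**What the plan says.** Under Cluster Randomized Trial Design, the 40 facilities "will be randomized to an (A) early or (B) delayed onset study arm". The same section adds: "From each cluster, 3 cohorts of 10 mother-child dyads (1 retrospective cohort and 2 prospective cohorts) will be enrolled into the study". The early arm contributes cohorts A1 (untreated), A2 and A3 (treated). The delayed arm contributes B1 and B2 (untreated) and B3 (treated).

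Under Quantitative Analysis of Intervention Effectiveness, robust standard errors are to cover "clustering of observations across mother-child dyads enrolled from the same geographic clusters at the same time". The last four words define the cluster as one facility in one enrollment round.

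Statistical Power uses the same unit: "This equates to k=120 statistical clusters with n=10 women per cluster". It continues: "Half of these clusters (k=60/120, 50%; n=600/1200, 50%) will be allocated to the intervention arm and half to the control arm".

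The effect is to be estimated by comparing mean outcomes of all treated with all untreated participants, and also by an accelerated failure time model with group membership as the main covariate. The design section likens the design to a difference-in-difference, but writes no equation and names no facility, arm or round terms.

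**The concern.** The facility is assigned once, and that single draw fixes the treatment status of all three of its cohorts. The cohorts also share the facility, its catchment area and its community health workers, so delays in A1, A2 and A3 of one facility are likely to be correlated. A sandwich estimator clustered on facility-by-round assumes that this correlation is zero. Clustering should be at the level of assignment, or at least at a level across which outcomes can be taken as independent.

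At stake is the calibration of the confidence interval and P value for the primary outcome. The article leaves the regression terms open, so a reader cannot tell from it whether the interval would be wasteful, about right or too short.

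**Working it through.** **Inputs from the article.** The primary outcome "has an SD of 28 days". There are 40 facilities with 3 cohorts of 10 each, 600 treated and 600 untreated children, and a target difference of 7 days. The ICC is 0.05 or 0.10.

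**Assumptions not in the article.** Two-sided alpha is 0.05. The share π of the ICC that persists across rounds within a facility is varied from 0 to 1. The treatment effect is constant. Linear regression on days stands in for the accelerated failure time model.

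**Step 1: reproduce the stated power.** The design effect is 1 + 9 × ICC, which is 1.45 or 1.90. The SE is 28 × √(2 × design effect / 600), which is 1.95 or 2.23 days. Power is Φ(7/SE − 1.96), which is 0.949 or 0.881. The article gives 0.95 and 0.88, so its power calculation does treat the 120 cells as independent.

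**Step 2: variance components of a cell mean.** With variance 28² = 784:
- facility part, shared by the three cohorts: f = 784 × ICC × π
- remainder: r = 784 × ICC × (1 − π) + 784 × (1 − ICC)/10

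**Step 3: pooled comparison.** Each cell has weight +1/60 or −1/60. An early facility enters as A2 + A3 − A1 and a delayed one as B3 − B1 − B2. The facility effect therefore has net weight ±1/60, not three separate contributions.
- True variance: (40f + 120r)/3600
- Variance counted by facility-by-round clustering: 120(f + r)/3600

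Example with ICC 0.05 and π = 1: f = 39.2 and r = 74.48. The true variance is (1568 + 8937.6)/3600 = 2.92, SE 1.71. The counted variance is 120 × 113.68/3600 = 3.79, SE 1.95.

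| ICC | π | True SE | Facility-by-round SE | Ratio |
|---|---|---|---|---|
| 0.05 | 0 | 1.95 | 1.95 | 1.00 |
| 0.05 | 0.5 | 1.83 | 1.95 | 1.06 |
| 0.05 | 1 | 1.71 | 1.95 | 1.14 |
| 0.10 | 0 | 2.23 | 2.23 | 1.00 |
| 0.10 | 0.5 | 2.02 | 2.23 | 1.10 |
| 0.10 | 1 | 1.80 | 2.23 | 1.24 |

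**Step 4: arm and round effects.** The contrast is (A2 − B2) − ½[(A1 − B1) + (A3 − B3)]. Within a facility the weights 1, −½, −½ sum to zero, so the facility effect cancels in truth but is still counted. The ratio is √((f + r)/r). For π of 0.5 and 1 it is 1.10 and 1.24 at ICC 0.05, and 1.16 and 1.45 at ICC 0.10.

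**Step 5: round effects only.** All first-round children are untreated and all third-round children are treated, so only A2 versus B2 informs the effect. Each facility then contributes one informative cohort, and the two clustering levels nearly coincide.

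**Step 6: simulation with estimated sandwich SEs** (at least 4,000 trials per scenario, no true effect). Estimated SEs run slightly below the closed forms because residuals shrink.
- Pooled, π from 0.5 to 1: too wide by about 5-11% at ICC 0.05 and 7-23% at ICC 0.10. A repeat with 40,000 trials per scenario gave 5-13% and 9-23%. Type I error falls to about 2-3% at high persistence.
- Arm and round effects: too wide by about 8-38%, up to 42% in the larger run.
- Round effects only: SE ratio 0.96-0.99, coverage 93.4-94.4%.
- Facility and round fixed effects, uncorrected sandwich: SE about 16-20% too small, type I error about 11-12%.
- Clustering on the 40 facilities: coverage 93.9-95.3% in every model.

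**The case against.** The strongest defence is that the analysis actually described, the pooled comparison, errs on the conservative side. Its interval is too wide and false positives fall below 5%, and if nothing persists across rounds there is no error at all. This stands. For that analysis the cost is lost precision, not a spurious positive result, and it limits how severe the point can be.

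A reader might infer that 120 clusters in place of 40 must make the interval too narrow, especially given the difference-in-difference analogy. The article does not support this. It writes no such model, and the version with arm and round effects errs the other way. The shortfall appears only when facility fixed effects are added with an uncorrected sandwich. Even there the cause is not ignored correlation: the SE is about as short at π = 0. Fitting 40 facility terms to three cells each shrinks residuals by roughly √(2/3) = 0.82, and a CR2 correction at the same facility-by-round level restores the type I error to about 5%.

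A reader might likewise infer that using 120 clusters overstates power. For the pooled contrast under these assumptions it does not: at π = 1 the true SEs of 1.71 and 1.80 days imply power of 0.984 and 0.974, above the stated 0.95 and 0.88. Power under a round-adjusted model is a separate question.

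Finally, the full protocol or analysis plan may say more. But the article does not leave the level open: it states one, and the power section uses the same one.

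**Conclusion.** The point holds in a limited form. The stated clustering level does not match the unit of randomization, and it is used consistently in the analysis and power sections. The pooled SE is too wide by roughly 5-14% at ICC 0.05 and 7-24% at ICC 0.10 if half to all of the facility effect persists, and is correct if none does. With arm and round effects it is too wide by about 8-45%, taking closed forms and simulation together. With round effects only it is nearly right.

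It would go too far to say that no analysis consistent with the design gives valid intervals, or that the trial faces an inflated false-positive rate as written.

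The figures rest on an assumed persistence share, linear regression on days and a constant effect. The last assumption matters for direction. If the effect varies between facilities, that component has true weight 2² + 1² = 5 per pair of early and delayed facilities, while facility-by-round clustering counts 3. This pulls the pooled SE the other way, so even the pooled direction is conditional. No accelerated failure time model was simulated.

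This should be fixed before analysis. It is not a fatal flaw.

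**What to change.** In Quantitative Analysis of Intervention Effectiveness, replace the sentence on robust standard errors with one that clusters on the randomized facility (40 clusters) across all three cohorts. Add a small-sample correction, either a t reference with about 38 degrees of freedom or CR2. Apply it to both the mean comparison and the accelerated failure time model.

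In Statistical Power, reconcile the 120-cluster wording: 40 facilities are randomized, and the 120 cells are facility-by-round groups, not independent units.

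The cost is one sentence, one line of code and fewer degrees of freedom. With a t reference on 38 degrees of freedom and no persistence, the stated power moves from 0.949 to 0.939 at ICC 0.05 and from 0.881 to 0.865 at ICC 0.10. Recruitment and data collection do not change.

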#### Analysis of Implementation Outcomes

We will generate summary measures (eg, means) for continuous data and use proportions to summarize categorical data. For outcomes assessed using validated measures (eg, the Acceptability of Intervention Measure [26]), we will present composite scale scores. Qualitative implementation outcomes will be analyzed as described below.

#### Analysis of Qualitative Data and Integration With Quantitative Data

Thematic analyses will be facilitated by qualitative software (eg, NVivo [Lumivero]) and a codebook made up of a priori and emergent structural codes based on the interview guide and 4 interrelated steps: reading, coding, data display, and data reduction [27]. The data will be used to fully map the Chanjo Kwa Wakati process from the perspectives of the mother and the CHW and characterize the opportunities and limitations of using digital and in-person resources to support vaccination timeliness. Using convergent mixed methods, we will use joint displays and narrative integration to connect the quantitative and qualitative data [28-30].

#### Analysis of Systematic Variation in Effectiveness

Extensive sensitivity analysis for the aim 1 primary and secondary outcomes analyses will characterize variation in intervention effectiveness with population, setting, and implementation factors. Variation in intervention effectiveness will be evaluated using interactions between geographic, maternal, or child characteristics and the intervention variable. Statistically significant parameters on interaction terms are indicative of differential intervention effects for different subgroups. To account for variation in implementation, sensitivity analysis will include per-protocol (as-treated) and intention-to-treat analyses in which a vector of variables describing the fidelity of the different intervention components will be used in place of the binary intervention variable.

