The second aim is to evaluate the implementation factors associated with variation in intervention effectiveness and develop an implementation blueprint for intervention scale-up to other settings. Study logs, fidelity checklists, quantitative surveys, and qualitative interviews with mothers and key informants will be used to inform other constructs of the RE-AIM framework, specifically reach, adoption, implementation, and maintenance. Two key implementation outcomes of interest are participants’ reports of the receipt of intervention components (intervention fidelity) and their reports of intervention acceptability. Analyses of variation in intervention implementation at the cluster level and systematic variation in the effectiveness for aim 1 outcomes across children will guide the future optimization of Chanjo Kwa Wakati. The results will be used to develop an implementation blueprint to guide future adaptations and scale-up of Chanjo Kwa Wakati.

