### Intervention Components

Chanjo Kwa Wakati focuses on individual-level barriers to timely vaccination to complement the Tanzanian government’s efforts to strengthen vaccination systems and reduce structural barriers [20]. Chanjo Kwa Wakati comprises the following individual-level intervention components: a vaccination knowledge intervention, reminders about upcoming vaccination due dates, service notifications, and conditional incentives for timely vaccination (Table 2). The intervention’s target population is the mother-child dyad from the time of pregnancy (third trimester) until the child is aged 1 year. Intervention activities are targeted toward the mother, whereas the timeliness of Penta3 (primary outcome) and other vaccinations recommended before age 1 year (secondary outcomes; Table 1) is assessed for the child.

**Table 2 table2:** The Chanjo Kwa Wakati intervention.

Timing	Activities	Detailed description of activities
Last trimester of pregnancy	Enrollment Registration in digital health system Knowledge intervention Baseline assessment^a^	Informed consent^a^ Register pregnancy and phone numbers in the digital health system Identify knowledge gaps for an individualized knowledge intervention based on a study by Vasudevan et al [6] Assess postintervention change in vaccination knowledge and attitudes as well as potential correlates of coverage and timeliness^a^
≤4 wk after the date of delivery	CHW^b^ phone call or home visit	Ascertain date and place of birth as well as the receipt of vaccinations due at birth Register the birth, record the 6-wk vaccination due date, and update phone numbers in the digital health system
Before each vaccination due date (6, 10, and 14 wk, and 9 mo)	SMS text message reminders with incentive offers Backup: CHW phone calls or home visits Knowledge intervention	Messages are sent to the mother and vaccine advocates 7 d and 1 d before each vaccination Messages are individualized and account for information on service interruptions Messages include conditional incentive offers Individualized knowledge intervention focused on vaccinations due at an upcoming visit
≤1 wk after each vaccination due date	CHW phone call or home visit	Verify vaccination status and date against vaccination card and issue incentive as appropriate Update vaccination due dates (and thus reminders) as necessary

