#### Incentive Offers

Conditional incentive offers will be specific to each child’s vaccination schedule. In our prior work [7,8], we identified a set of incentives (eg, pharmacy vouchers and birth certificates) that are likely to be acceptable to mothers. The specific incentives, their value, conditionality, and the timing of disbursement will be determined in discussion with local key informants.

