### Intervention Activities

Figure 1 describes the sequence of intervention activities. Pregnant women, enrolled in their third trimester, will receive a home visit from a CHW before the birth of their child, be registered with the Chanjo Kwa Wakati digital health system, and receive an individualized knowledge intervention to screen and counsel for common knowledge gaps and concerns about routine childhood vaccinations. After the birth of the child, the mother will receive individualized SMS text message reminders for upcoming vaccinations, messages aimed at mitigating persistent vaccination knowledge gaps, service notifications (eg, related to stockouts or service nonavailability), and conditional economic incentive offers aimed at encouraging timely vaccinations. CHWs will use the digital health system for work planning, recording vaccination dates and due dates, and following up on missed vaccination appointments and backstop the digital health system with phone calls and in-person visits as needed for vaccination reminders and assessing and addressing mothers’ knowledge gaps.

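### A sensitivity analysis labelled intention-to-treat replaces assignment with fidelity variables, and some of these would be driven by the outcome if they record incentive receipt or missed-visit follow-up

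*Protocol article*

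**What the plan says.** Under Analysis of Systematic Variation in Effectiveness the article states that "sensitivity analysis will include per-protocol (as-treated) and intention-to-treat analyses in which a vector of variables describing the fidelity of the different intervention components" stands in for assignment; the fidelity vector, on this plan, "will be used in place of the binary intervention variable". The term intention-to-treat appears nowhere else in the article. Other sections bear on what the fidelity variables could be:

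- **Study Overview and Aims (Aim 2)** describes one key implementation outcome as participants' "reports of the receipt of intervention components (intervention fidelity".
- **Intervention Components** lists, besides the knowledge intervention, "reminders about upcoming vaccination due dates, service notifications, and conditional incentives for timely vaccination". In Table 2, within a week after each due date, the community health worker (CHW) is to "Verify vaccination status and date against vaccination card and issue incentive as appropriate" and to "Update vaccination due dates (and thus reminders) as necessary".
- **Incentive Offers** leaves the terms open: "The specific incentives, their value, conditionality, and the timing of disbursement will be determined in discussion with local key informants".
- **Intervention Activities** gives CHWs the task of "following up on missed vaccination appointments".
- **Quantitative Analysis of Intervention Effectiveness** compares intervention and nonintervention groups, and takes group membership as the main covariate in the regression.

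Aim 2 adds that analyses of variation in implementation and effectiveness will guide later optimisation of the intervention.

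**The concern.** There are three separate problems.

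1. **Label.** Intention-to-treat means analysis by assignment. Replacing the assignment variable with what was received gives a non-randomised comparison under a randomised name.
2. **Merged terms.** Per-protocol usually excludes children whose delivery departed from plan; as-treated reclassifies children by what they received. The article uses one as a gloss on the other. This matters because External Events sends the stockout question to the per-protocol analysis.
3. **Direction of cause.** An incentive paid for timely vaccination follows from timeliness, and follow-up of a missed appointment follows from lateness. If either is a regressor for delay, its coefficient largely restates the outcome.

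At stake is the component-level message. Such a model could credit incentive payments and penalise CHW follow-up when neither has any effect, and so feed a misleading signal into the optimisation work.

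**Working it through.** **Step 1: order in time.** Using Table 2, Intervention Activities and Vaccination Reminder Messages:

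| Exposure | Timing | Depends on Penta3 delay? |
|---|---|---|
| Prenatal knowledge session | Before birth | No; ordinary confounding only |
| Reminder with incentive offer | 7 days and 1 day before the due date | Not on this dose's delay, though due dates may be revised after earlier doses |
| Routine CHW contact | Within 1 week after the due date | No; planned for all |
| Incentive issued | After status and date are checked | Yes, if payment requires timeliness |
| Missed-appointment follow-up | After a missed appointment | Yes |

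The Follow-Up Survey collects implementation measures 12 to 15 months after birth, from intervention women only. Reported receipt is therefore recorded after Penta3 timing is known.

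**Step 2: the plan's own figures.** Statistical Power gives SD 28 days, a 7-day difference, 120 cluster-phases of 10 children, and 600 children per group. No alpha is stated; two-sided 0.05 is assumed.
- ICC 0.05: design effect 1 + 9 × 0.05 = 1.45; effective n = 600/1.45 = 413.8; SE = 28 × √(2/413.8) = 1.95; power = Φ(7/1.95 − 1.96) = 0.949, against 0.95 stated.
- ICC 0.10: design effect 1.90; effective n = 315.8; SE = 2.23; power 0.881, against 0.88 stated.

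These figures reproduce. They do not concern the fidelity analysis, but they supply the SD and the 7-day yardstick.

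**Step 3: closed-form illustration with zero effect.** Assume exponential delays, and an incentive paid to every intervention child vaccinated within 28 days.

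*Calibrated to the 47.8% rural Penta3 delay in Background:*
- Mean = 28/ln(1/0.478) = 37.9 days.
- Mean if later than 28 days = 37.9 + 28 = 65.9. Mean if within 28 days = (37.9 − 0.478 × 65.9)/0.522 = 12.3.
- Within intervention children, the gap is 65.9 − 12.3 = 53.6 days.
- The trial also has 600 controls who receive no incentive. There are 0.478 × 600 ≈ 287 intervention non-recipients. The comparator mean is (600 × 37.9 + 287 × 65.9)/887 = 47.0, so the gap is 47.0 − 12.3 ≈ 35 days.

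*Calibrated to the plan's SD of 28 (exponential mean 28):*
- The proportion later than 28 days is e⁻¹ = 0.368. Means are 56 (late) and (28 − 0.368 × 56)/0.632 = 11.7 (timely).
- The comparator mean is (600 × 28 + 221 × 56)/821 = 35.5, so the gap is about 24 days.

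**Step 4: simulation on the trial layout.** 120 groups of 10, normal delays, SD 28, ICC 0.05, linear regression of delay with cluster-robust SEs, 200 replicates per setting. Assumptions not in the documents: mean delay 14 or 28 days; incentive paid if vaccinated within 7 or 28 days; follow-up if still unvaccinated at 7 days; delivery 70% or 95%; reminder received by 85%, unrelated to outcome.

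| Coefficient (days) | True effect 0 | True effect −7 |
|---|---|---|
| Assignment alone | 0.01 to 0.22 | −6.8 to −7.2 |
| Incentive received (vector model) | −22 to −37 | −19 to −37 |
| Missed-visit follow-up (vector model) | +11 to +30 | +9 to +31 |

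With mean delay 28, a 28-day window and 95% delivery, the incentive coefficient is −33.4 under no effect and −32.4 under a true 7-day benefit. It hardly responds to the truth. With the true 7-day benefit, the reminder coefficient is about −6 when entered alone, but −1.5 to −5.7 beside the two outcome-driven variables.

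**The case against.** The strongest reply is that the article lists no variables for the vector, and that coding choices in a sensitivity model belong in an analysis plan that is not shown. Incentives are repeatedly described as offers, sent before the due date; coded that way, the item is not caused by the outcome. Chasing missed visits is a CHW activity and not one of the four named components. The blueprint also draws on logs, checklists, interviews and cluster-level variation, so one regression would not decide it. Finally, the sentence might be meant to attach the vector only to the per-protocol analysis.

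Most of this stands, and it limits the point. It does not remove it. The label is wrong in the text as printed. If another meaning was intended, the sentence still needs rewording. Aim 2 speaks of receipt, which leaves the outcome-driven coding open and perhaps likely.

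A reader might infer that every coefficient in the vector would be an artefact. The documents do not support that: the prenatal session, the reminders and the routine contact are not triggered by a late Penta3 dose, and their problem is confounding.

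**Conclusion.** The point holds for the wording and, conditionally, for bias. As printed, an analysis without the assigned group is called intention-to-treat, and two different received-treatment analyses are merged. If the vector includes incentive receipt or missed-visit follow-up, their coefficients are driven by the outcome. With no true effect and controls included, incentive receipt would appear to cut delay by about 22 to 37 days, some three to five times the 7-day design difference. Follow-up would appear to add about 11 to 30 days.

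The direction was the same in every setting tried. The sizes depend on the assumed delay distribution, payment window and delivery rates. They also come from a linear model of days, whereas the article's multivariable analysis uses accelerated failure time models.

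Two stronger readings go too far. One is that the trial loses its randomised estimate; the main analysis is by assigned group and is untouched by this point. The other is a spurious gap of about 54 days. That contrast is confined to intervention children, its exponential has an SD of 38 days against the plan's 28, and it falls to about 35 days once controls are included.

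**What to change.** - Reserve intention-to-treat for the comparison already given under Quantitative Analysis of Intervention Effectiveness: all children, by assigned facility-by-phase status.
- Name and define per-protocol and as-treated separately, and say which one addresses stockouts.
- Label the fidelity model exploratory and non-randomised.
- Limit its variables to exposures fixed before the due date (reminder sent, incentive offered, prenatal knowledge session done) or to cluster-level delivery rates. For Penta3, take the due date as the nominal 14-week date, because revised dates can carry earlier lateness.
- Exclude incentive payment and missed-visit follow-up.
- If an effect of treatment received is wanted, assignment can serve as an instrument for overall receipt only. One binary instrument cannot separate several components.

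The cost is analysis wording, plus a check that the digital system or study logs record when reminders and offers were sent, which the article does not state. The downside is that the model no longer gives an association for incentive payment or for missed-visit follow-up.
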